### Statistical analyses and sample size calculation

The statistical analysis will be performed by an independent statistician using SAS 9.3 (SAS Institute, Inc., Cary, NC, USA). For the primary endpoint, the effect of a drug on ΔTF will be estimated using generalized estimating equations (GEEs) and a multiple linear regression model adjusting for time of the measurement and baseline TF of the right side. This hemidiaphragm has been chosen because it is more easily identified for the presence of the liver. For the secondary endpoint, the association between a drug and its collateral effect will be evaluated using a logistic regression model. *P* values lower than 0.05 have been considered statistically significant.

Finally, descriptive statistics of all variables describing the characteristics of the patients enrolled in the study and those excluded from the study will be analyzed. Continuous variables will be expressed as mean (± standard deviation, (SD)) and median (ranging from 25th to 75th percentiles). Percentages will be calculated for dichotomous data. For categorical variables, frequency counts and percentages will be calculated.

Since this is the first clinical trial that proposes, as its primary endpoint, a relative reduction of 30% in the incidence of residual curarization, the necessary sample size has been calculated using the statistical software Epi Info (version 7). This analysis shows that at least 30 patients per group will be necessary, considering that in 5% of subjects TF is not valuable [22, 23], and expecting 23–25% of residual curarization with neostigmine 30 min after the extubation vs. 2–4% after the administration of sugammadex (with a 95% confidence interval (CI) and a power of 80%, and assuming equal variance between the two groups). For the secondary outcome, the number needed to treat has been calculated with a CI of 95%.

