Sugammadex is the first selective reversal agent for steroidal NMBAs. It has been shown to give full and rapid recovery of muscle strength, thus minimizing the occurrence of PORC [8, 10].

The diaphragm, the major respiratory muscle in humans, is a great septum between the thoracic and abdominal cavities. The movement of the diaphragm accounts for 60–70% of the total tidal volume of respiration. Failure of diaphragmatic function is believed to play a central role in the pathophysiology of the clinical syndrome known as “pump respiratory failure” [11–13]. Although a TOF ratio > 0.9 in the adductor pollicis rules out residual curarization, the diaphragm is often not evaluated in the operating room. The diaphragm is the most highly resistant muscle to NMBAs, as well as the first to recover [14], but the occurrence of its dysfunction has been implicated in postoperative respiratory failure, especially when mechanical ventilation is prolonged [15, 16]. Therefore, studying diaphragmatic function in a perioperative context is extremely important.

Since 1985, ultrasonography has been used to evaluate diaphragm function by measuring thickness variations in the apposition zone, which reflect the extent of contraction of the muscle [17]. Vivier et al. recently demonstrated that the thickening fraction (TF), namely the difference between the thickness at the end of inspiration (TEI) and that at the end of expiration (TEE), normalized for TEE (TEI – TEE/TEE), is directly related to respiratory workload, and they suggested that TF could be used as an index to select those patients ready to be weaned from non-invasive ventilation [18]. These data suggest that ultrasound TF could also be used in different scenarios, and our purpose is to use ultrasound TF to assess diaphragm recovery after dNMB since it is more comfortable for conscious patients than acceleromyography.

We therefore hypothesize that the incidence of postoperative diaphragmatic dysfunction, assessed using ultrasonography and, from our unpublished observations, defined by a fractional shortening of the diaphragm < 40%, is lower in patients who receive sugammadex than in those who receive neostigmine.

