**Fig. 2 Fig2:**
[figure not shown]
Study flow diagram

In the case of unexpected events, such as a change in drug dose or a participant’s request to withdraw from the study, the protocol will be stopped and this will be recorded on the case report form (CRF). No further tests will be performed except those necessary to finalize the protocol. Should patients need medical care that interferes with the correct conduct of the study, they will be excluded from the study.

The primary endpoint of the study will be a 30% relative reduction in the incidence of residual curarization in patients who receive sugammadex compared with neostigmine 30 min after drug administration. The primary endpoint will be assessed at 30 min because the effects of neostigmine start to fade after this time has elapsed [20]. Residual curarization will be determined by the percentage of 30 min TF compared to baseline TF. It is not known exactly what percentage TF indicates residual curarization, but from our unpublished observations, values of 40% or less could indicate diaphragmatic dysfunction. However, we do not know what percentage of patients have a TF < 40% when neostigmine is administered.

Two secondary endpoints will be assessed. One secondary endpoint will be a 10% relative reduction in respiratory complications related to residual curarization obtained with sugammadex compared with neostigmine. Respiratory complications taken into consideration will be new cough and sputum production, abnormal breath sounds not present at baseline, temperature higher than 38 °C, chest radiography documentation of atelectasis or new infiltrates, and physician documentation of atelectasis or pneumonia [21]. The other secondary endpoint will be a 30% relative decrease in postoperative nausea or vomiting in patients who receive sugammadex compared with those who receive neostigmine.

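### The primary hypothesis, endpoint and sample size concern an incidence at 30 min, but the analysis named for the primary endpoint is a linear model of continuous ΔTF

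*Protocol article*

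**What the plan says.** Three parts of the protocol article set the primary question as a proportion.

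- **Hypothesis (Background, last paragraph):** "We therefore hypothesize that the incidence of postoperative diaphragmatic dysfunction", defined by a cut-off of 40%, is lower with sugammadex.
- **Primary endpoint (Intervention plan, endpoint paragraph after Fig. 2):** "The primary endpoint of the study will be a 30% relative reduction in the incidence of residual curarization", assessed at 30 min.
- **Sample size (Statistical analyses and sample size calculation):** at least 30 per group, from expected rates of 23–25% with neostigmine and 2–4% with sugammadex, 80% power, a 95% confidence level and 5% of subjects without a usable TF.

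The same statistics section then names the analysis for the primary endpoint. The response is ΔTF, and the drug effect on it "will be estimated using generalized estimating equations (GEEs) and a multiple linear regression model", adjusted for measurement time and right-side baseline TF. Logistic regression, the only explicitly binary-outcome model named, is assigned to the secondary endpoint. Percentages for dichotomous data appear only among the descriptive statistics.

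On case definition, the endpoint paragraph says: "Residual curarization will be determined by the percentage of 30 min TF compared to baseline TF". It then offers 40% or less as a value that could indicate dysfunction and admits that the right percentage is not known.

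**The concern.** An endpoint and its analysis should address the same quantity. Here the endpoint is the share of patients who are cases at one time, and the analysis estimates a difference in the mean of a continuous change. The article gives no step that turns ΔTF into a case of residual curarization, and it names neither a 30-min contrast nor a drug-by-time term.

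Two things are at stake. First, if the analysis is run as described, the primary P value will concern mean ΔTF and cannot confirm or refute the incidence hypothesis. Second, the power statement that justifies 60 patients belongs to a comparison that the article does not name as an analysis. The Trial status section says that data collection is complete and analysis is about to start, so little time remains to settle this without knowledge of results.

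**Working it through.** **1. Type of each element**

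| Element | Quantity | Time |
|---|---|---|
| Hypothesis | proportion below 40% | postoperative |
| Primary endpoint | relative reduction in incidence | 30 min |
| Sample size | two proportions | 30 min |
| Named primary analysis | mean ΔTF (GEE, linear regression) | all scans, adjusted for time |

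The first three agree with each other; the fourth differs in quantity and in time. A GEE can take a binary response with a logit link, but the response named is ΔTF and the companion model is linear.

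**2. Why one quantity does not give the other.** Suppose every sugammadex patient had a TF higher by a constant and nobody in either arm was below the cut-off. The mean difference would be that constant and the incidence difference zero. Conversely, 23–25% of 30 is about 7 to 7.5 neostigmine cases; if the other neostigmine patients had slightly higher values, the means could coincide while the incidences differed. This shows that the two can disagree, not how likely that is.

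**3. The plan's own figure.** Two-proportion formula with pooled variance under the null, two-sided α = 0.05 (sidedness is not stated), 80% power:

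n = [1.96·√(2p̄(1−p̄)) + 0.8416·√(p₁(1−p₁)+p₂(1−p₂))]² / (p₁−p₂)²

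- 25% vs 2%: p̄ = 0.135; (0.947 + 0.383)² / 0.23² = 33.4, so 34; 34/0.95 gives 36.
- 23% vs 4%: p̄ = 0.135; (0.947 + 0.391)² / 0.19² = 49.6, so 50; 50/0.95 gives 53.

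The range is 36–53 per group after allowing for 5% unusable scans (45–64 with continuity correction). The stated 30 is not reproduced two-sided. One-sided without continuity correction it is matched at 24% vs 2% (28, then 30 after inflation), with the full range 29–42.

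**4. Power for proportions at 30 per group, two-sided**

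Power = Φ{[(p₁−p₂)√n − 1.96·√(2p̄(1−p̄))] / √(p₁(1−p₁)+p₂(1−p₂))}

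- 25% vs 2%: (1.260 − 0.947)/0.455 = 0.687, power 75%.
- 23% vs 4%: (1.041 − 0.947)/0.464 = 0.201, power 58%.

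Fisher's exact test gives 63% and 41%. With 28 evaluable per group (0.95 × 30 = 28.5) the figures are 55–72%, and 36–57% by Fisher.

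**5. Power for the named analysis.** With 30 per group, 80% power at a single time point requires a standardized difference of about (1.96 + 0.8416)·√(2/30) = 0.72. The article gives no ΔTF difference or standard deviation, so this cannot be turned into a TF value or compared with the 80% claim. Repeated scans and baseline adjustment could lower it by an unknown amount.

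**6. What an incidence analysis would still need**

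- **Cut-off:** 40% is applied to the fraction itself in the hypothesis and, apparently, to TF relative to baseline in the endpoint paragraph.
- **Time origin:** the 30 min run from drug administration (endpoint paragraph), extubation (sample size) or leaving the operating theater (scan schedule).
- **Effect size:** the planning rates imply a relative reduction of 1 − 4/23 = 83% to 1 − 2/25 = 92%, not 30%. For a 30% reduction from 23–25% (to 16.1–17.5%), power at 30 per group is about 10%.

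**The case against.** The best defence is that a continuous analysis is sensible here. The Abstract states the primary objective as comparing the drugs' effects on residual curarization and does not mention incidence. The endpoint paragraph bases residual curarization on a percentage of baseline and concedes that no cut-off is established. Modelling baseline-adjusted change in TF is then defensible, and it generally uses more information than a dichotomy. This stands as a reason to prefer one repair over the other. It does not reconcile the text, because the endpoint and the sample size are still worded as an incidence.

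A second defence is that the statistical analysis plan mentioned in the data-sharing statement may contain the missing comparison. That limits the claim. A reader might infer that the incidence question will never be tested; the document at hand shows only that this article names no such test. But the article is not silent on the primary analysis: it names one, and that one does not fit.

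A reader might also infer that the investigators could pick between two primary results. The article does not support this, since it names a single response variable for the primary analysis and assigns the work to an independent statistician. Nor does the low expected sugammadex count (30 × 0.02–0.04 = 0.6–1.2 events) show a mismatch. It bears only on which method suits a comparison of proportions, and only at the planning rates.

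**Conclusion.** The point holds as a contradiction within the article: hypothesis, endpoint and sample size are binary at 30 min, while the analysis named for the primary endpoint is continuous and spans measurement times. Its drug coefficient does not estimate a reduction in incidence, and the 80% power statement does not apply to it. This should be resolved before analysis.

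The conclusion rests on the wording alone and not on the sample-size arithmetic. The 58–75% power figure assumes a two-sided 0.05 test, 30 evaluable patients per group and the article's planning rates. The documents do not support the stronger conclusion that modelling ΔTF is itself wrong; either quantity could serve as primary if endpoint, analysis and power statement agree.

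**What to change.** Before unblinding, adopt one of two options and report it as a change made after data collection.

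**(a) Keep the incidence endpoint.** Make the comparison of proportions at one fixed 30-min scan the primary analysis, for example a risk difference with a score confidence interval and an exact test, since few sugammadex events are expected at 2–4%. Keep baseline-adjusted ΔTF as a supportive analysis. First fix one case definition (40% of TF itself, or of baseline TF) and reconcile the three time origins. Restate power for the planning rates as about 58–75% two-sided at 30 per group, lower with Fisher's test.

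**(b) Keep the model.** Redeclare baseline-adjusted right-side ΔTF at 30 min as the primary endpoint, define ΔTF, and name the 30-min drug contrast. Drop the incidence claim and its 80% power statement, and report incidence as secondary.

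The cost is revised wording, one further analysis and, under (a), a less favourable stated power; under (b), the stated power is given up. No new data are needed.

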At the end of the operation and when TOF neuromuscular monitoring shows a minimum of two twitches, patients will receive the reversal drug according to the group to which they have been randomized. Patients in the NEO group will receive 50 μg/kg neostigmine and 15 μg/kg atropine, while those in the SUG group will receive 2 mg/kg sugammadex [19]. The drugs will be prepared for intravenous injection in identical volumes and in indistinguishable syringes so that the anesthesiologist will be blinded to the treatments the patients receive. Extubation will be performed when all the following criteria are met: (1) the patient is awake and can execute simple commands; (2) the patient’s respiratory pattern is regular with a tidal volume of 6–7 mL/kg referred to ideal body weight; (3) the TOF ratio is > 0.9. Immediately prior to extubation, bilateral diaphragm ultrasonography will be performed to assess muscle recovery in spontaneously breathing patients; these measurements will be compared to the baseline muscle assessment. Two additional diaphragm ultrasound scans will be performed 10 and 30 min after discharge from the operating theater under the same conditions as described above, but no further TOF monitoring will be carried out. Follow-up will be performed to document adverse events and complications until discharge from the hospital. The physician who performs the ultrasound scan will be different from the one who administers the reversal drug and will be blinded to the treatment that patients receive (Figs. 1 and 2). The Standard Protocol Items: Recommendations for Interventional Trials (SPIRIT) checklist is provided as Additional file 1.

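### The primary endpoint is set at 30 min, but the stated model gives one drug effect averaged over three scans and names no 30-min contrast

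*Protocol article*

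**What the plan says.** The paragraph on endpoints (protocol article, Intervention plan, after Fig. 2) defines the primary endpoint as "a 30% relative reduction in the incidence of residual curarization in patients who receive sugammadex compared with neostigmine 30 min after drug administration". It gives a reason for the time point: "The primary endpoint will be assessed at 30 min because the effects of neostigmine start to fade after this time has elapsed".

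The Intervention plan schedules three scans after baseline. The first: "Immediately prior to extubation, bilateral diaphragm ultrasonography will be performed to assess muscle recovery". The others: "Two additional diaphragm ultrasound scans will be performed 10 and 30 min after discharge from the operating theater".

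The section Statistical analyses and sample size calculation states the primary model: "For the primary endpoint, the effect of a drug on ΔTF will be estimated using generalized estimating equations (GEEs", together with multiple linear regression, "adjusting for time of the measurement and baseline TF of the right side". Time therefore appears as an adjustment term. The section does not mention an interaction of drug with time, a contrast at one scan, or a restriction to the 30-min scan.

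**The concern.** Adjusting for time of measurement makes sense only if several scans per patient enter the model. With drug, time and baseline TF as terms, there is one drug coefficient, common to all the post-baseline scans, while the endpoint belongs to one of them. The two agree if the drug effect is the same at every scan. If it is not, the main result answers a different question from the one the trial poses. It may understate or overstate the 30-min difference, and its power may be lower or higher than that of a 30-min comparison. Leaving the contrast unnamed also leaves open a later choice between a pooled and a 30-min result.

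**Working it through.** **The plan's own figure.** The article gives no SD, within-patient correlation, time profile or power for ΔTF, so there is no figure on this point to reproduce. Its 80% power and 30 patients per group refer to a binary incidence (23–25% versus 2–4%). A two-sided pooled comparison of proportions without continuity correction needs 34–50 per group before the 5% allowance, so 30 is not reproduced that way. That is a separate matter, and nothing below depends on it.

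**Inputs from the article.** Three post-baseline scans; 30 per group; significance at 0.05, taken as two-sided because a 95% confidence interval is used.

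**Assumptions.** ΔTF is change from baseline. Variance is equal at the three scans, with exchangeable correlation ρ between a patient's scans, ρ = 0.3, 0.5 or 0.7, and data are complete. The 30-min contrast alone has 80% power. The effect at each scan is expressed as a fraction of the 30-min effect, under four profiles.

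**Formulas.**
- Averaged effect relative to the 30-min effect: m = mean of the three fractions.
- Variance of the average relative to one scan: v = (1 + 2ρ)/3, which gives 0.533, 0.667 and 0.800.
- A contrast with 80% power has an expected z of 1.96 + 0.84 = 2.80. Power of the averaged coefficient = Φ(2.80 × m/√v − 1.96).

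Worked case, effect at 30 min only, ρ = 0.3: m = 1/3, √v = 0.730, m/√v = 0.456, and Φ(2.80 × 0.456 − 1.96) = Φ(−0.68) = 0.248.

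| Effect before extubation, 10 min, 30 min | m | Power, ρ = 0.3 | ρ = 0.5 | ρ = 0.7 |
|---|---|---|---|---|
| 0, 0, 1 | 0.33 | 24.8% | 20.7% | 18.0% |
| 0, 0.5, 1 | 0.50 | 48.3% | 40.3% | 34.7% |
| 0.5, 0.75, 1 | 0.75 | 82.0% | 73.0% | 65.1% |
| 1, 1, 1 | 1.00 | 97.0% | 92.9% | 87.9% |

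The reference is 80% in every cell.

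**Check by simulation.** 30 per arm, correlation 0.5, 300 replicates, true 30-min effect 0.75 SD. Mean estimates:

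| True effects | Drug + time + baseline | With drug×time, contrast at 30 min |
|---|---|---|
| 0, 0, 0.75 | 0.26 | 0.76 |
| 0, 0.375, 0.75 | 0.38 | 0.76 |
| 0.75, 0.75, 0.75 | 0.76 | 0.74 |

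The model as described recovers the 30-min effect only in the constant case. The interaction model recovers it in all three.

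**The case against.** The article is a condensed account and refers to a separate analysis plan and code. An interaction or a visit contrast could stand there, so it cannot be said that the analysis will lack one. This stands as a limit on certainty. It does not remove the point, because the article commits to a primary model, lists its covariates, and gives time only the role of adjustment.

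A reader might infer that the protocol itself expects a difference growing from scan to scan, with the least before extubation because every patient has by then passed a TOF ratio of 0.9. The text does not say this. Its rationale is that neostigmine begins to fade after 30 min. The Background credits sugammadex with fast and complete recovery, which allows an early difference. The abstract's aim of detecting concealed residual block implies that a satisfactory TOF ratio at the thumb need not mean equal diaphragm function in the two arms. The time profile is unknown, so the low-power rows of the table cannot be quoted alone. Under a constant effect the pooled coefficient does better than the 30-min contrast.

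A reader might also take the mention of multiple linear regression as a second, ordinary regression on stacked scans, with type I error inflated by ignoring the correlation. The plainer reading is a GEE with a linear mean model, since both share one covariate list. The documents do not support a claim of inflated type I error.

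**Conclusion.** The point holds as a mismatch between a single-time endpoint and a model whose drug coefficient, as described, averages over three post-baseline scans. That conclusion needs no assumption about SD or correlation. The consequence does: power of the averaged coefficient runs from 18% to 97% against a reference of 80%, and the documents give no basis for choosing within that range. The figures are illustrations and do not predict that the trial would miss a real effect. The mismatch should be corrected before analysis.

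Two related matters remain even with the right contrast. The endpoint is a binary incidence while the model is for continuous ΔTF, so a 30-min contrast on mean ΔTF does not estimate that incidence. The 30 min also has three starting points: giving the reversal drug (endpoint paragraph), extubation (sample size paragraph) and leaving the theater (scan schedule).

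**What to change.** Under Trial status, the article says data collection is complete and analysis has yet to start, so the change can still be made without sight of results.

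- Fit one GEE clustered by patient: ΔTF on drug, categorical time, drug×time and right-side baseline TF. State that the linear regression is the mean model of this GEE.
- Name the drug contrast at the 30-min scan as the primary ΔTF result. Report the other two scans as supportive.
- Apply the same 30-min contrast to the binary residual-curarization endpoint, so that the incidence named as primary is itself estimated.
- Reconcile the three reference points for 30 min, and state which one the analyzed scan represents.

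The cost is about one line of model specification. The downside is precision if the effect is in fact constant: the standard error is larger than that of the pooled coefficient by 1/√0.800 = 1.12 to 1/√0.533 = 1.37, that is 12–37%, and power is 80% where the pooled coefficient would have 88–97%.

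### Thirty patients per group does not give the stated 80% power across the protocol's own rates under a two-sided 5% test

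*Protocol article*

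**What the plan says.** The sizing statement is in the protocol article, Statistical analyses and sample size calculation. It names Epi Info version 7 and concludes, with an allowance for unusable scans: "This analysis shows that at least 30 patients per group will be necessary, considering that in 5% of subjects TF is not valuable". The rates are given as "expecting 23–25% of residual curarization with neostigmine 30 min after the extubation vs. 2–4% after the administration of sugammadex". The error levels are "with a 95% confidence interval (CI) and a power of 80" per cent, followed by "assuming equal variance between the two groups". Earlier in the same section the significance threshold is set: "values lower than 0.05 have been considered statistically significant".

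Study design and eligibility fixes 60 patients in total, and Randomization fixes 1:1 allocation, so 30 per group is the whole trial. The article does not say which formula was used, whether the test is one- or two-sided, or which pair of rates within the ranges produced 30.

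The endpoint text at the end of Intervention plan, after Fig. 2, says of the neostigmine rate: "we do not know what percentage of patients have a TF < 40% when neostigmine is administered".

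**The concern.** Every input needed to check the sample size is printed, and so is the output, but they do not agree on the ordinary reading. A 95% confidence level with a 0.05 threshold normally means a two-sided 5% test. On that reading 30 per group looks too few for rates of this size, before any scans are lost.

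Data are collected and analysis is about to start (Trial status), so this sentence will shape how the result is read. A reader told that the trial had 80% power may take a non-significant difference in incidence as fairly firm evidence against a difference of the planned size. If power was nearer 64%, a true difference of 24% vs 3% would be missed about 36% of the time, not 20%.

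**Working it through.** **Inputs (all from the protocol article).** α = 0.05, taken as two-sided; power 80%; neostigmine rate p₁ = 23–25%; sugammadex rate p₂ = 2–4%; 5% not evaluable; 1:1 allocation; 30 per group. Normal quantiles: 1.960 (two-sided 5%), 0.842 (80% power).

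**Attempt to reproduce 30.** Pooled two-proportion formula, with p̄ = (p₁ + p₂)/2:

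n = [1.960·√(2p̄(1−p̄)) + 0.842·√(p₁(1−p₁) + p₂(1−p₂))]² / (p₁ − p₂)²

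Midpoint, 24% vs 3%: p̄ = 0.135, so √(2 × 0.135 × 0.865) = 0.4833. Also √(0.1824 + 0.0291) = 0.4599. Then n = (0.9472 + 0.3871)² / 0.21² = 1.780 / 0.0441 = 40.4, or 41 evaluable per group.

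The same average rate, 0.135, applies at both extreme corners:
- 25% vs 2%: n = 33.4, or 34.
- 23% vs 4%: n = 49.6, or 50.

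Dividing by 0.95 gives 35.2, 42.5 and 52.2, or 36, 43 and 53 to randomise. Rounding up to 41 before dividing makes the middle figure 44.

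**Other two-sided formulas, evaluable per group (after dividing by 0.95 where shown).**

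| Method | 25% vs 2% | 24% vs 3% | 23% vs 4% |
|---|---|---|---|
| Pooled | 33.4 (35.2) | 40.4 (42.5) | 49.6 (52.2) |
| Pooled, continuity-corrected | 41.7 | 49.4 | 59.6 |
| Average-p | 34.7 | 41.6 | 50.8 |
| Unpooled | 30.7 (32.3) | 37.6 (39.6) | 46.9 (49.3) |
| Arcsine | 26.9 (28.4) | 34.4 (36.2) | 43.9 (46.3) |

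Only the arcsine formula comes in at about 30 after loss, and only at 25% vs 2% (28.4) and 24% vs 2% (28.7 before loss, 30.2 after).

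**One-sided 5%.** The pooled formula gives 26.2 at 25% vs 2%, 27.8 at 24% vs 2%, 29.6 at 23% vs 2% and 29.7 at 25% vs 3%, all before loss. At 24% vs 3% it gives 31.7 (33.3 after loss), and at 23% vs 4% it gives 38.9 (41.0). The one-sided arcsine formula does fit within 30 at the midpoint (27.1, or 28.5 after loss), but not at 23% vs 4% (34.6, or 36.4).

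**Power of the size actually used.** 30 × 0.95 = 28.5, so about 28 evaluable per group. The pooled normal approximation at 24% vs 3% is:

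Φ[(0.21 × √28 − 0.9472) / 0.4599] = Φ(0.357) = 0.639

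| Two-sided 5% | 25% vs 2% | 24% vs 3% | 23% vs 4% |
|---|---|---|---|
| Pooled normal, n = 28 | 72.3% | 63.9% | 55.0% |
| Pooled normal, n = 30 (no loss) | 75.4% | 67.1% | 58.0% |
| Exact, uncorrected chi-square, n = 28 | 81.4% | 71.3% | 60.5% |
| Exact, Fisher, n = 28 | 57.2% | 46.1% | 36.1% |

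**Equal variance.** A binomial variance is fixed by its rate: 0.24 × 0.76 = 0.18 against 0.03 × 0.97 = 0.03, about a sixfold difference.

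**The case against.** The strongest reply is that 30 is attainable. The two-sided arcsine formula gives it at 25% or 24% vs 2%. A one-sided test gives it at several pairs and, with the arcsine formula, at the midpoint. An uncorrected chi-square test has exact power of 81% with 28 per group at 25% vs 2%. All of this stands. A reader might infer that no standard method yields 30 anywhere in the stated range, and the calculations do not support that. What the reply does not rescue is the sentence as printed. It gives ranges, not the best corner, and mentions no one-sided test. No two-sided method examined supports 30 at the midpoint, and no method examined, one-sided or two-sided, supports it at 23% vs 4% after loss.

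Second, these powers belong to a comparison of two proportions. The same section analyses the primary endpoint as ΔTF, with generalized estimating equations and linear regression adjusted for time and baseline TF. A reader might infer that this regression has only 55–72% power. The article gives no effect size or variance for ΔTF, so its power cannot be computed either way. The point is confined to the sizing statement.

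Third, a reader might see a contradiction between the admission that the neostigmine rate is unknown and the use of 23–25%. There is none of substance: the sizing sentence presents the rates as expectations, and planning on an assumed value for an unknown rate is normal.

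Finally, the trial is closed to recruitment, so the correction changes no patient, endpoint or analysis. That limits the consequence, but it does not make the stated power right.

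**Conclusion.** The sizing statement is not reproducible from its own inputs under a two-sided 5% test. By the pooled formula the requirement is 34–50 evaluable per group, against 30 randomised, and every pair of rates in the range falls short of 80% even with no loss (best case 75.4%). After 5% loss, power is 55–72% by that approximation, 61–81% for an exact uncorrected chi-square and 36–57% for Fisher. Of these, only the uncorrected chi-square at 25% vs 2% reaches 80%.

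The conclusion rests on three assumptions: that 95% confidence with a 0.05 threshold means two-sided testing; that the stated rates are taken across their ranges; and that the 5% loss falls equally on both groups. If the calculation was in fact one-sided, or used only the most favourable rate pair, 30 could be explained, but the article would then have to say so. The equal-variance phrase is wrong for these rates under any reading.

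**What to change.** Do not enrol more patients. Replace the sizing sentence with one that:

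- states the test, its sidedness and the rate pair behind the figure of 30, if the original calculation can be recovered;
- gives the power of the fixed size. For example: 30 randomised (about 28 evaluable) per group give about 55–72% power for 23–25% vs 2–4%, and 64% at 24% vs 3%, by the pooled normal approximation at two-sided 5%. The corresponding exact power is 61–81% for an uncorrected chi-square and 36–57% for Fisher's test;
- deletes the equal-variance assumption;
- says that this power refers to the binary comparison of incidence and not to the ΔTF regression.

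The cost is one reworded paragraph and a less favourable power figure. Conduct, endpoints and analysis are unaffected. The results report should use the corrected figure, and should put the confidence interval for the difference in incidence ahead of any reading of a non-significant result.
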